## CONVERT Statistical Analysis Plan

The analysis will be based on intention-to-treat principles (ITT). Patient data will be grouped by treatment arm according to the treatment assignments made via the MAHSC-CTU randomisation line. The primary data analysis is planned for January 2015.

The stratification factors include centre, PS (0–1 vs 2) and biochemical factors (eg, LDH, sodium, alkaline phosphatase). Comparison of data by centre will be scrutinised to identify any data inconsistencies, it will also be used to identify those centres planning to give either four or six cycles of chemotherapy. Analysis will be carried out to identify any differences between the two schedules. Other factors have been identified in previous studies to be prognostic factors and will be used to calculate the Manchester score, which gives three groupings of good, intermediate and poor prognosis; these scores will be used to compare OS and response rate.

The only planned interim analyses have been performed for the Independent Data Monitoring Committee (IDMC). Reports have been submitted to the IDMC on an annual basis starting 12 months after the first patient was randomised.

The following are the qualifications for analysis of time-to-event efficacy parameters:

- All randomised patients will be included in the analysis of overall survival (OS) and local progression free survival (ITT).

OS is the time between date of randomisation and date of death of any cause. Survivors will be censored on the last date known to be alive. Local progression-free survival (local control) will be calculated from the date of randomisation to the date of first clinical evidence of progressive disease at the primary site, or death. Kaplan-Meier curves will be drawn for each treatment group. Overall survival and local progression-free survival will be compared using the Mantel-Cox version of the log rank test.

- All randomised patients treated with at least one study dose of cisplatin and etoposide will be included in the comparison of proportions of grade 3 and 4 toxicities.

Toxicity will be assessed according to NCI Common Terminology Criteria for Adverse Events V.3.0. The proportion of patients experiencing a grade of 3 or above acute toxicity, including acute and/or late radiation morbidity, will be compared between the treatment groups using  $\chi^2$  and Fisher Exact tests. Acute toxicity will be defined as toxicities occurring from commencement to 3 months after completion of treatment; late toxicity will be defined as toxicities occurring between 3 months and 2 years after completion of treatment. All patients treated with at least one dose of cisplatin and etoposide will be evaluated for tumour response and included in the analysis of tumour response rates.

Response will be assessed according to Response Evaluation Criteria In Solid Tumours (RECIST) criteria. The proportion of patients in each treatment group whose best response (up to approximately 28 days post cycle 4 or, if stopped prior to cycle 4, approximately 28 days after last chemotherapy cycle given) from randomisation is complete or partial will be compared using  $\chi^2$  and Fisher Exact tests.

Safety analyses will be performed for all randomised patients treated with at least one dose of chemotherapy. Adverse effects will be summarised and compared between the two arms. The relative chemotherapy and RT dose intensity (RDI) will be summarised by calculating the median, SD, IQR and range for patients in each randomised treatment group. The RDI will be compared between the treatment groups by using the Wilcoxon Rank Sum test.

A detailed description of patient disposition will include a summary of the following:

- ▶ All patients entered and enrolled: overall, by treatment arm and by country
- ▶ Reasons for patients entered but not enrolled
- ▶ All enrolled patients treated with study drug, by treatment arm
- ▶ Reasons patients enrolled but not treated with study drug
- ▶ Reasons patients discontinued study drug treatment
- ▶ All important protocol violations.

## CONVERT Statistical Analysis Plan

The analysis will be based on intention-to-treat principles (ITT). Patient data will be grouped by treatment arm according to the treatment assignments made via the MAHSC-CTU randomisation line. The primary data analysis is planned for January 2015.

The stratification factors include centre, PS (0–1 vs 2) and biochemical factors (eg, LDH, sodium, alkaline phosphatase). Comparison of data by centre will be scrutinised to identify any data inconsistencies, it will also be used to identify those centres planning to give either four or six cycles of chemotherapy. Analysis will be carried out to identify any differences between the two schedules. Other factors have been identified in previous studies to be prognostic factors and will be used to calculate the Manchester score, which gives three groupings of good, intermediate and poor prognosis; these scores will be used to compare OS and response rate.

The only planned interim analyses have been performed for the Independent Data Monitoring Committee (IDMC). Reports have been submitted to the IDMC on an annual basis starting 12 months after the first patient was randomised.

The following are the qualifications for analysis of time-to-event efficacy parameters:

- All randomised patients will be included in the analysis of overall survival (OS) and local progression free survival (ITT).

OS is the time between date of randomisation and date of death of any cause. Survivors will be censored on the last date known to be alive. Local progression-free survival (local control) will be calculated from the date of randomisation to the date of first clinical evidence of progressive disease at the primary site, or death. Kaplan-Meier curves will be drawn for each treatment group. Overall survival and local progression-free survival will be compared using the Mantel-Cox version of the log rank test.

- All randomised patients treated with at least one study dose of cisplatin and etoposide will be included in the comparison of proportions of grade 3 and 4 toxicities.

Toxicity will be assessed according to NCI Common Terminology Criteria for Adverse Events V.3.0. The proportion of patients experiencing a grade of 3 or above acute toxicity, including acute and/or late radiation morbidity, will be compared between the treatment groups using  $\chi^2$  and Fisher Exact tests. Acute toxicity will be defined as toxicities occurring from commencement to 3 months after completion of treatment; late toxicity will be defined as toxicities occurring between 3 months and 2 years after completion of treatment. All patients treated with at least one dose of cisplatin and etoposide will be evaluated for tumour response and included in the analysis of tumour response rates.

Response will be assessed according to Response Evaluation Criteria In Solid Tumours (RECIST) criteria. The proportion of patients in each treatment group whose best response (up to approximately 28 days post cycle 4 or, if stopped prior to cycle 4, approximately 28 days after last chemotherapy cycle given) from randomisation is complete or partial will be compared using  $\chi^2$  and Fisher Exact tests.

Safety analyses will be performed for all randomised patients treated with at least one dose of chemotherapy. Adverse effects will be summarised and compared between the two arms. The relative chemotherapy and RT dose intensity (RDI) will be summarised by calculating the median, SD, IQR and range for patients in each randomised treatment group. The RDI will be compared between the treatment groups by using the Wilcoxon Rank Sum test.

A detailed description of patient disposition will include a summary of the following:

- ▶ All patients entered and enrolled: overall, by treatment arm and by country
- ▶ Reasons for patients entered but not enrolled
- ▶ All enrolled patients treated with study drug, by treatment arm
- ▶ Reasons patients enrolled but not treated with study drug
- ▶ Reasons patients discontinued study drug treatment
- ▶ All important protocol violations.

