### 7.2 General Considerations

For data analyses, patient data will be grouped by treatment arm according to the treatment assignments made via the Christie Hospital randomization line (described in Section 3.3).

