**Radiotherapy RDI:**

Relative dose intensity (RDI) is defined as the dose intensity achieved by a patient relative to a schedule that would have given the intended radiotherapy on a fixed 45 day schedule for OD and 19 day schedule for BD. The duration of the radiotherapy for this calculation will run from the first day of radiotherapy to the last day of the radiotherapy. The RDI will therefore be calculated as:

$$\left( \frac{\text{totaldose}_{\text{AT}}}{\text{totaldose}_{\text{PT}}} \right) \left( \frac{\text{time}_{\text{PT}}}{\text{time}_{\text{AT}}} \right)$$

where  $\text{totaldose}_{\text{AT}}$  is the actual total dose received and  $\text{totaldose}_{\text{PT}}$  is the respective planned total dose received.

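### Toxicity and radiotherapy dose intensity are grouped by assigned arm only, with no as-received table and no stated reference schedule for a patient given the other radiotherapy

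*Supplement*

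**What the plan says.** The SAP opens with a rule for all analyses: "Patient data will be grouped by treatment arm according to the treatment assignments made via the MAHSC-CTU randomisation line". Protocol version 3, Section 7.2, agrees: "patient data will be grouped by treatment arm according to the treatment assignments made via the Christie Hospital randomization line". Neither document makes an exception for safety or dose intensity.

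The SAP then defines who is counted:

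- Toxicity at grades 3 and 4: "All randomised patients treated with at least one study dose of cisplatin and etoposide will be included in the comparison of proportions of grade 3".
- Safety: "Safety analyses will be performed for all randomised patients treated with at least one dose of chemotherapy", followed by "Adverse effects will be summarised and compared between the two arms".
- RDI: "summarised by calculating the median, SD, IQR and range for patients in each randomised treatment group", with a Wilcoxon rank sum test between groups.

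The RDI formula is in protocol Section 7.5, not in the SAP. It measures the radiotherapy delivered against "the intended radiotherapy on a fixed 45 day schedule for OD and 19 day schedule for BD". It does not say which schedule is the intended one for a patient who changes schedule.

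**The concern.** The safety sets already depart from pure intention to treat, because they require treatment received. But the treatment they require is chemotherapy, which both arms share. The randomised difference is the radiotherapy schedule, and it affects neither who is counted nor where. Radiation oesophagitis and pneumonitis follow from the schedule delivered, and protocol Section 5.1 treats both as serious at grades 3 and 4.

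No blinding is described, and once-daily and twice-daily treatment are plainly distinguishable, so a patient could end up on the other schedule. The plan has no rule for that case. Assigned-arm grouping would then place the patient's radiation toxicity under the schedule not received, which pulls the two arms together. For a toxicity comparison that is the less cautious direction. In the RDI, a complete course could enter as a value far from 100% that says nothing about how well it was delivered.

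**Working it through.** **Inputs.** Twice daily (BD): 45 Gy in 30 fractions; once daily (OD): 66 Gy in 33 fractions (protocol 4.2.2). Optimal times 19 and 45 days (4.3.1, 4.4.1). RDI = (dose received / dose planned) × (time planned / time taken) (7.5). Grade 3 oesophagitis 27% BD and 11% OD, from the earlier randomised trial cited in the Background.

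**1. The plan's reference times reproduce.** Monday start, five treatment days a week:

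- OD: 33 fractions = 6 full weeks (42 days) + 3 days = 45 days.
- BD: 30 fractions at two a day = 15 treatment days = 2 full weeks (14 days) + 5 days = 19 days.

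**2. RDI of a complete course of the other schedule**, if the planned values are those of the assigned arm:

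- Assigned BD, given 66 Gy in 45 days: (66/45) × (19/45) = 0.619, or 62%.
- Assigned OD, given 45 Gy in 19 days: (45/66) × (45/19) = 1.615, or 161%.

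If the planned values are those of the schedule delivered, both courses score 100%: (66/66) × (45/45) and (45/45) × (19/19).

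**3. Effect on mean RDI.** Let a share c of each arm switch and every other course score 100%. The OD-arm mean is (1 − c) + 1.615c and the BD-arm mean is (1 − c) + 0.619c.

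| c (assumed) | OD arm | BD arm |
|---|---|---|
| 1% | 100.6% | 99.6% |
| 5% | 103.1% | 98.1% |
| 10% | 106.1% | 96.2% |

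The SAP reports median, SD, IQR and range. At a few percent the median and the rank test move little; the SD and range are more exposed.

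**4. Effect on a toxicity difference.** Assume switchers carry the average risk of the schedule they receive. Then BD arm = 0.27(1 − c) + 0.11c, OD arm = 0.11(1 − c) + 0.27c, and the difference is 0.16(1 − 2c).

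| c each way (assumed) | Difference, points |
|---|---|
| 0% | 16.0 |
| 1% | 15.7 |
| 2% | 15.4 |
| 5% | 14.4 |
| 10% | 12.8 |

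The once-daily group in the cited trial received 45 Gy, not 66 Gy, so these rates illustrate the mechanism and do not forecast this trial.

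**5. Other provisions.** Protocol 4.9 plans a sub-analysis that excludes patients with protocol violations; it does not regroup them, and the SAP does not repeat it. The disposition summary is framed around study drug. Protocol 7.10 covers omissions, reductions and delays. A change of schedule might be listed as an important protocol violation, but the toxicity and RDI tables would stay as they were.

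**The case against.** A reader might infer from protocol 4.9 that a patient who misses the planning limits may be moved to the other schedule, since the decision is left to the local investigator. The text does not support that: the adjustment it recommends is a lower total dose. The delay rules in 4.3.3 and 4.4.3 aim to complete the assigned total dose. No section describes or provides for a change of schedule. This objection stands: switching is possible but is not something the plan anticipates.

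A reader might also take 62% and 161% as what the plan would certainly report. They depend on reading the planned dose and time as those of the assigned arm. That is the natural reading beside summaries by randomised group, but Section 7.5 does not settle it. What is established is an undefined reference.

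Finally, protocol 3.4 says that the trial compares treatment policies. Under that aim, toxicity by assigned arm is a legitimate, randomised comparison, and an as-received table is not: if changes of schedule followed from tumour volume or planning limits, the as-received groups would be confounded. This stands too. It argues for showing both tables, not for replacing one by the other.

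**Conclusion.** The point holds as a modest gap. Toxicity, adverse effects and RDI are grouped by assigned arm only, the safety sets take no account of the radiotherapy received, and the RDI reference is undefined for a patient given the other schedule. Grouping overall survival and local progression-free survival by assigned arm is right and is not in question.

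The size is unknown because the documents give no switch rate. In the example the loss is 0.6 points of 16 at 2% each way and 3.2 points at 10%; with no switching there is none. The example rests on borrowed event rates, equal switching in both directions and average risk among switchers. The documents do not support a claim that the toxicity comparison is seriously biased or that the Wilcoxon test is materially distorted. The case for acting is that the omission is cheap to repair and concerns two secondary endpoints, toxicity and radiotherapy dose intensity.

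**What to change.** In the SAP:

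1. Keep assigned-arm grouping for the efficacy analyses.
2. Present grade 3 or higher toxicity and adverse effects twice: by assigned arm, and by radiotherapy schedule actually started. Patients who start no radiotherapy stay in their assigned arm. State that the second table is not a randomised comparison.
3. Define the planned dose and time in the radiotherapy RDI as the full protocol values of the schedule started (66 Gy in 45 days or 45 Gy in 19 days), so that a reduced total dose still lowers the score.
4. Report the number of schedule changes by assigned arm.

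The cost is a few sentences, one further toxicity and adverse-effect table and one line of counts. The radiotherapy worksheet (Form C, protocol 6.5) is already collected, and the RDI already needs the dose received and the first and last treatment dates, so little or no new data should be required. The drawback is possible confounding in the as-received table, which is why the assigned-arm table stays beside it.

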### 3.4 RANDOMISATION

Randomisation will be administered centrally by the trials office at the Christie Hospital. This is a multi-centre randomized phase III trial. Patients will be randomized on a 1:1 basis to one of two treatment arms. The allocation method will be minimization with a random element. Randomisation will be implemented in a bespoke computer application at the randomisation centre. The factors controlled for in the allocation will be:

Institution  
Planned number of cycles (4 or 6)  
Performance status (0/1 or 2) {PS2 equivalent to KP 50, 60}

The arm that would result in less imbalance will be allocated with probability 0.75. There will be a 'burn-in' period of 20 cases in which allocation will be completely random.

Randomisation can only be performed **after** confirmation that the patient is eligible (including recording of LDH, sodium and alkaline phosphatase results) and that the patient has signed consent. The system used does not permit any editing of fields by users after arm allocation has been performed.

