### 4.1 CHEMOTHERAPY

Patients should start chemotherapy within two weeks of randomisation and within two weeks of a clinical assessment of fitness (section 4.1.1). Chemotherapy is cisplatin and etoposide and is given for 4 to 6 cycles. One cycle is given prior to radiotherapy. The second cycle in both arms is given concurrently with radiotherapy if possible. Radiotherapy will start on day 22 of cycle 1. In the BD radiotherapy arm, the third to sixth cycles (if applicable) are given after completion of the thoracic radiotherapy. In OD radiotherapy arm, the third & fourth cycles of PE are also given concurrently and the fifth & sixth cycles (if applicable) are given after completion of the thoracic radiotherapy.

Centres will be given the choice to stop chemotherapy after 4 cycles or to continue to up to 6 cycles. Centres who decide to give 6 cycles will have to continue doing so for all patients entered in the trial (unless it is decided that it is not in the patients best interest to receive cycle 5 and 6 or due to patient's choice)

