***Overall survival and local progression-free survival.***

Overall Survival is the time between date of randomisation and date of death of any cause. Survivors will be censored on the last date known to be alive. **Local progression-free survival (local control)** will be calculated from the date of randomisation to the date of first clinical evidence of progressive disease at the primary site, or death.

Kaplan-Meier curves (Kaplan and Meier 1958) will be drawn for each treatment group. Overall survival and local progression-free survival will be compared using the Mantel-Cox version of the log rank test.

- All randomized patients treated with at least one study dose of cisplatin and etoposide will be included in the comparison of proportions of grade 3 and 4 toxicities.

**Toxicity** will be assessed according to NCI Common Terminology Criteria for Adverse Events v 3.0 (see appendix 2). The proportions of patients experiencing a grade of 3 or above acute toxicity, including acute radiation morbidity, or late radiation morbidity will be compared between the treatment groups using Chi-squared and Fisher Exact tests. Acute toxicity will be defined as toxicities occurring from commencement of treatment to 3 months after completion, late toxicity will be defined as toxicities occurring between 3 months and 2 years after completion of treatment.

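### The SAP's stratification factors do not match the protocol's minimisation factors, and no use of the minimisation factors is stated for the primary log-rank test; the cost is modest (about 0 to 4 points of power)

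*Supplement*

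**What the plan says.** **Allocation (protocol 3.4).** "The allocation method will be minimization with a random element". The factors are institution, "Planned number of cycles (4 or 6") and PS (0/1 or 2). After a burn-in of 20 patients, "The arm that would result in less imbalance will be allocated with probability 0.75". LDH, sodium and alkaline phosphatase must be recorded before randomisation as part of confirming eligibility. They are not in the list of allocation factors.

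**SAP.** "The stratification factors include centre, PS (0–1 vs 2) and biochemical factors (eg, LDH, sodium, alkaline phosphatase"). Planned cycles is not on this list. The next sentences use centre to identify which sites plan four or six cycles, and then: "Analysis will be carried out to identify any differences between the two schedules". The Manchester prognostic groups are to be used to compare OS and response, with no method given.

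**Primary test (protocol 7.3.1, repeated in the SAP).** "Overall survival and local progression-free survival will be compared using the Mantel-Cox version of the log rank test". Neither document states strata, covariates or a Cox model for OS.

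**Cycles (protocol 4.1).** "Centres will be given the choice to stop chemotherapy after 4 cycles or to continue to up to 6 cycles". A centre that opts for six must keep to six for all its patients, with exceptions for patient interest or choice.

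**The concern.** A plan should let two analysts reach the same primary p-value. Here one analyst could run a plain log-rank test, another could stratify by the SAP list, and a third by the factors actually used for allocation. The SAP names stratification factors without saying what they are for, and two of its three entries (centre and PS) overlap with the minimisation factors while the third does not.

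Minimisation makes the arms more alike on the chosen factors than simple randomisation would. A test that does not use those factors takes no credit for that balance: its variance is somewhat too large if the factors are prognostic, so it tends to be conservative and to lose some power. Following the SAP list literally is not clearly better, since it brings in centre, which may split the data into many small strata.

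A secondary matter is the planned look at the two chemotherapy schedules. The number of cycles is a centre policy, so a direct comparison mixes its effect with differences between centres.

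**Working it through.** **1. The two lists side by side**

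| Factor | Minimisation (protocol 3.4) | SAP stratification factors |
|---|---|---|
| Institution / centre | yes | yes |
| PS (0-1 v 2) | yes | yes |
| Planned cycles (4 or 6) | yes | no; read off centre |
| LDH, sodium, alkaline phosphatase | no; recorded only | yes, as examples |

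The superseded version 1 protocol allocated on cycles and PS, so the biochemical values were not allocation factors there either. The SAP wording closely follows version 1 section 7.12, which the change log says was deleted when minimisation came in.

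**2. The plan's own figures (protocol 7.1)**

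Inputs: two-sided 5%, 80% power, hazard ratio (HR) 0.70, 2-year survival 44% v 56%.

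- Freedman deaths: (1.960 + 0.842)² × [(1 + 0.70)/(1 − 0.70)]² = 252.04, so 253.
- Mean 2-year death rate: (0.56 + 0.44)/2 = 0.50. Patients: 253/0.50 = 506, as stated.
- Schoenfeld deaths: 4 × (1.960 + 0.842)²/(ln 0.70)² gives 247, the stated number.
- 506 × 1.05 = 531.3, so 532, as stated.

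The figures reproduce. Neither formula has a term for strata, and the sample size is not at issue.

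**3. What the choice of test does**

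From the documents: 532 patients, probability 0.75, burn-in of 20, the three minimisation factors, analysis at 247 deaths, HR 1 or 0.70, control survival based on 44% at 2 years.

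Assumed, because the documents do not give them: 70 centres of unequal size, half giving six cycles, cycles fixed within centre, uniform 4-year accrual, exponential survival, imbalance taken as the sum of marginal differences, and all prognostic effects.

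Statistic: Z = Σ(a − p)/√Σp(1 − p), summed over deaths within each stratum. Here a indicates the experimental arm and p is that arm's share of those at risk in the stratum. There were 3,000 trials per cell; the Monte Carlo standard error is about 0.4 points for type I error and 0.8 for power.

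| PS 2 share, PS HR, cycles HR, centre SD (log hazard) | Type I: plain / PS × cycles | Power: plain / PS × cycles / PS × centre |
|---|---|---|
| 3%, 1.5, 1.0, 0 | 5.2% / 5.1% | 79.0% / 79.1% / 69.5% |
| 5%, 2, 1.0, 0.2 | 5.1% / 5.3% | 79.1% / 78.9% / 68.4% |
| 15%, 2, 1.2, 0.3 | 4.7% / 4.8% | 75.2% / 76.4% / 64.0% |
| 25%, 2.5, 1.3, 0.5 | 4.1% / 4.7% | 67.7% / 71.6% / 59.6% |

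- Gain from PS × cycles over plain: 0.1, −0.2, 1.2 and 3.9 points.
- Cost of PS × centre relative to PS × cycles: 9.6, 10.5, 12.4 and 12.0 points.

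**4. A second simulation**

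This used 8,000 trials per cell, 70 centres and 2-year follow-up. With PS 2 in 5-10%, PS HR 2, cycles HR 0.85-1 and centre SD 0-0.2, the plain test had type I error of 4.4-4.6%, and stratifying gained 0.4-1.2 points of power. In the strongest cells (PS 2 in 20%, PS HR 2.5, centre SD 0.3) the figures were 3.8-3.9% and 2.8-3.9 points.

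Across both sets, the plain test's type I error is 3.8% to 5.2% and the power loss about 0 to 4 points.

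**The case against.** **The SAP does not say that the test is unstratified.** This stands. A reader might infer that the plan prescribes a test that ignores the allocation factors. The documents show only that no use of them is specified. The supported fault is an ambiguity about the primary test, together with a list that differs from the protocol's.

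**The list may not be meant as a list of allocation factors.** This stands in part. The words *include* and *eg* leave it open, and version 1 kept its allocation factors and its stratification factors in separate sections. But an SAP that uses the term without giving a purpose, after the protocol dropped its own stratification section, needs correcting on either reading.

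**Planned cycles is not absent from the SAP.** This stands. It is read off centre and, by protocol 4.1, is largely fixed within centre. It is missing only from the list of factors.

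**The biochemical values are not wrong variables.** This stands. They are known before randomisation and are a sound choice as prognostic covariates; only the label is wrong.

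**The loss is small and assumption-driven.** This stands. PS 2 patients enter only by exception (3.3.2), and the protocol's background says evidence on four against six cycles is insufficient, so the strong-factor settings may not apply. A reader might infer a markedly conservative test or a certain loss of power. Neither is supported: a smaller simulation (1,500 trials per setting) gave 3.3-3.7% type I error in its stronger settings, but the two larger ones did not go below 3.8%, and with weak factors there is no loss.

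**Stratifying by PS and cycles also leaves out a minimisation factor.** True. Leaving institution out of the strata is a judgement, supported by the cost of sparse strata shown above, and the SAP should state it.

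**The sentence on four and six cycles makes no causal claim.** True. It gives no endpoint or test, so one cannot say that the trial would present it as evidence on chemotherapy duration. It is a labelling point.

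**Conclusion.** The point holds in a limited form. The SAP's factor list differs from the protocol's minimisation factors: planned cycles is missing and biochemical values are added. Neither document says whether or how the minimisation factors enter the primary OS test.

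Read as a plain log-rank, the test is valid and can be slightly conservative: type I error about 3.8% to 5.2% and a power loss of about 0 to 4 points, near zero if PS 2 is rare and cycles and centre have little effect. No inflation of false positives follows. Stratifying by PS and centre would cost more, about 10 to 12 points relative to PS by cycles.

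These sizes rest on assumed numbers of centres (70), PS 2 share and prognostic effects. The mismatch of lists and the silence about the test do not depend on them. The comparison of four with six cycles is a secondary point.

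**What to change.** In the SAP:

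1. Replace the list of stratification factors with the three minimisation factors: institution, planned cycles (4/6) and PS (0-1/2). List LDH, sodium and alkaline phosphatase separately as prognostic covariates.
2. Make the primary OS test a log-rank test stratified by planned cycles × PS (four strata), with the HR and 95% confidence interval from the matching stratified Cox model.
3. State that institution is left out of the strata because many centres will be small. Handle it in a supporting Cox model with institution as a random effect, adding the biochemical covariates.
4. Label any direct comparison of four with six cycles as non-randomised and descriptive. Examine cycles through a treatment-by-planned-cycles interaction.

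The cost is SAP wording only. Every factor is recorded at or before randomisation, and the sample size and event target are unchanged. The change should be made before the primary analysis, which the SAP plans for January 2015.

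### The SAP's stratification factors are not the trial's minimisation factors, and the survival log-rank uses neither set; the test is valid and the loss small, but the SAP text needs correcting

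*Supplement*

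**What the plan says.** **Allocation.** Protocol version 3, section 3.4: "The allocation method will be minimization with a random element". The list introduced by "The factors controlled for in the allocation will be" has three entries: institution; "Planned number of cycles (4 or 6"); and "Performance status (0/1 or 2) {PS2 equivalent to KP 50, 60"}. "The arm that would result in less imbalance will be allocated with probability 0.75", after a burn-in of 20 patients. LDH, sodium and alkaline phosphatase (ALP) appear in that section only as results to be recorded when eligibility is confirmed.

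**Analysis plan.** The SAP, printed twice in the Supplement with the same text, gives the stratification factors as centre, PS (0–1 v 2) and "biochemical factors (eg, LDH, sodium, alkaline phosphatase"). Planned cycles is not listed. It enters through the comparison of data by centre: "it will also be used to identify those centres planning to give either four or six cycles of chemotherapy", followed by an analysis of differences between the two schedules. The Manchester score is to be used in comparing OS and response, with no method stated.

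**Primary test.** "Overall survival and local progression-free survival will be compared using the Mantel-Cox version of the log rank test". Protocol section 7.3.1 names the same test. Neither document gives strata, covariates or a model for the hazard ratio.

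**The concern.** An analysis plan should describe the allocation that took place and say whether the analysis takes account of it. This one does neither. Its list matches the Stratification section (7.12) of the first protocol, which the record of changes says was deleted when minimisation came in. The text survived in the SAP.

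Three things are at stake. The report could state wrongly that the arms were balanced on three blood results. The planned number of cycles would be reconstructed from centre although it was fixed for each patient at allocation. And with a stratification list that matches neither the allocation nor the stated test, and a prognostic score to be used in an unstated way, the choice of adjusted analysis stays open until outcomes are known. A smaller point is precision: a test that ignores balanced prognostic factors tends to be slightly conservative.

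**Working it through.** **1. The lists side by side**

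| Factor | Used in allocation (protocol 3.4) | SAP stratification list | Used in the OS test |
|---|---|---|---|
| Institution / centre | yes | yes | no |
| Planned cycles, 4 or 6 | yes | no (read off from centre) | no |
| PS 0–1 v 2 | yes | yes | no |
| LDH, sodium, ALP | no (eligibility check) | yes | no |

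**2. The plan's own figures** (protocol 7.1: two-sided 5%, 80% power, HR 0.70, 2-year survival 44% v 56%)

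- Freedman deaths: (1.96 + 0.8416)² × (1.70/0.30)² = 252.04, so 253. The mean 2-year death probability is (0.56 + 0.44)/2 = 0.50, and 253/0.50 = 506 patients, as stated.
- Schoenfeld deaths: 4 × (1.96 + 0.8416)²/(ln 0.70)² gives 247, the stated number of deaths.
- 506 × 1.05 = 531.3, so 532, as stated.

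None of these formulas contains strata or covariates. The design calculation therefore assumes an unstratified log-rank, and the correction changes no sample-size figure.

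**3. Simulation of the protocol's minimisation**

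From the documents: 532 patients, three factors, probability 0.75, burn-in 20, control hazard from 44% survival at 2 years, HR 0.70, 4 years' accrual, analysis at the 247th death. Assumed: number and size of centres, prognostic effects, PS 2 in 10% (rows 1–2) or 15% (rows 3–4), and planned cycles set by centre. There were 4,000 runs per cell. All entries are percentages.

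| Centres; PS 2 HR; 6 v 4 cycles HR; SD of centre log-hazard | Type I error, unstratified | Type I error, PS × cycles | Power, unstratified | Power, PS × cycles | Power, centre × PS |
|---|---|---|---|---|---|
| 40; 1; 1; 0 | 4.2 | 4.6 | 80.5 | 80.6 | 72.4 |
| 40; 1.5; 1.2; 0.2 | 4.4 | 4.7 | 76.8 | 76.6 | 68.8 |
| 70; 2; 1.3; 0.4 | 4.7 | 5.4 | 73.5 | 75.5 | 63.6 |
| 70; 2; 1.3; 0.7 | 3.8 | 4.0 | 65.1 | 66.9 | 62.6 |

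The Monte Carlo standard error of a 5% rate is √(0.05 × 0.95/4,000) = 0.34 points.

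- Type I error of the unstratified test is 3.8–4.7%. With longer fixed follow-up, giving about 417–440 deaths under the null (2,000 runs), it was 3.3–4.9%. It never exceeds 5%.
- Stratifying by PS and planned cycles changes power by −0.2 to about +2 points.
- In the last row both tests stay below 5%, because centre, the strongest factor there, is in neither.
- Using every centre as a stratum (with PS) costs 2.5 points (65.1 − 62.6) to 9.9 points (73.5 − 63.6).

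**4. Adding the blood results**

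A second simulation used 532 patients, 253 deaths, 70 centres, assumed prognostic HRs of 1.25 to 2.0 and 2,500 trials per scenario (mild, moderate, strong).

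| Power, % | Mild | Moderate | Strong |
|---|---|---|---|
| Unadjusted log-rank | 79.2 | 76.8 | 74.7 |
| Log-rank stratified by PS × cycles | 79.0 | 76.4 | 75.2 |
| Cox with PS, cycles, LDH, sodium, ALP | 79.4 | 78.1 | 77.6 |

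Against the unadjusted test, stratifying gives −0.2, −0.4 and +0.5 points; the Cox model gives +0.2, +1.3 and +2.9. In the strong scenario the type I error was 4.6%, 4.6% and 5.2% respectively.

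**The case against.** The best defence is that the primary test is prespecified, identical in protocol and SAP, and the one the sample size assumes. It is valid: no simulated type I error for it exceeds 5%. Matching the allocation factors buys almost no power, and the larger gain comes from blood results that were never balanced, so it is a general argument for covariate adjustment and not a cost of the mismatch. Planned cycles is partly covered: protocol 4.1 makes it a centre policy with individual exceptions, and the SAP lists centre and plans to compare the schedules. The Manchester score is at least a stated route for prognostic factors. Annual IDMC reports had already been submitted when the SAP was written, so changing the primary test needs care. All of this stands, and it limits the weight of the point. It does not make the SAP's list correct or say how the score will be used.

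Three stronger readings are tempting and not supported:

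- **That ignoring the minimisation inflates false positives or invalidates the log-rank.** The simulated error is at or below nominal. An unadjusted hazard ratio nearer 1 reflects the difference between marginal and covariate-conditional effects; it does not bias the test of no difference.
- **That the trial will lose much power by stratifying on centre, PS and biochemistry.** The SAP does not specify such a test. Its log-rank carries no strata, so that loss is not a consequence of the plan.
- **That a Cox model including the three blood results must become the primary analysis.** The mismatch concerns PS, planned cycles and institution and does not reach that far. Eligibility criterion 3.3.2(j) also admits at most one adverse biochemical factor, which limits the prognostic spread to be gained from.

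**Conclusion.** The concern holds as a wrong statement in the SAP with a small analytic cost. The SAP names three factors that were not used in allocation, leaves planned cycles off its list, and compares OS and local PFS with a log-rank that is unadjusted because nothing else is specified. The test is valid and at most mildly conservative, with type I error of about 4–5% at 247 deaths. Stratifying by PS and planned cycles is worth −0.4 to about +2 points of power; adjusting for the blood results as well is worth up to about 3.

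The mismatch in the lists is certain, since it can be read off the documents. The sizes are not: they depend on assumed prognostic hazard ratios, centre numbers (40–70) and centre heterogeneity. The main reason to act is to describe the allocation correctly and fix the adjustment set in advance; extra power is secondary.

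**What to change.** - Replace the SAP's stratification sentence with the section 3.4 factors: institution, planned cycles (4 or 6) and PS (0–1 v 2). Take planned cycles as recorded for each patient at allocation, not inferred from centre.
- Compare OS and local PFS with the log-rank stratified by PS and planned cycles (four strata), and give a hazard ratio from a Cox model stratified in the same way. Report the unstratified log-rank alongside. Protocol 7.3.1 carries the same test wording, so amend it too or state that the SAP supersedes it.
- Do not use centre as a stratum, because the strata would be sparse. Examine it in a sensitivity analysis with a centre random effect.
- Call LDH, sodium and ALP, or the Manchester score, prognostic covariates. Prespecify one adjusted Cox analysis that uses them, with their coding stated; the cut-points in eligibility criterion 3.3.2(j) are one option.

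The cost is a dated SAP amendment before database lock and before the January 2015 analysis, made by people who have not seen outcomes by arm in the IDMC reports. No new data are needed, and the sample size and stated number of deaths do not change.
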